### Data Analysis

Basic hypothesis:

H1: Decrease (or lower increase) of the BDI-II and HDRS sum scores at T1 compared to baseline in the intervention group compared to the control group.H0: The changes in the BDI-II and HDRS sum scores between baseline and T1 do not differ between the intervention and the control group.

For the statistical analysis, we will use tools provided by the software packages IBM SPSS statistics and R (R Core Team). The changes in the symptom severity, as well as physiological parameters between baseline and T1 measurements, will be assessed. When comparing the change scores in the intervention group with those of the control group, typical hypothesis-testing, including mixed linear models, will be used, as provided by the software packages IBM SPSS statistics and R with a significance level of .05.

Sample size estimation: The estimation is based on an expected effect size of Cohen *d*=0.50, which is based on prior published studies of mindfulness-based apps. When setting the significance criterion α=.05 and β=.2 (statistical power 80%), the required sample size for a two-sample *t* test is 64 for each group. The dropout rate is expected not to exceed 10%, resulting in 140 patients overall.

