### Study Design

This study will be a single-center, open-label and randomized wait-list-controlled trial, which will take place at the University Psychiatric Clinics (UPK) Basel (Switzerland).

Participants will be randomly allocated to two conditions: (1) MBI mobile application Headspace+ TAU (intervention group) and (2) waitlist + TAU (control group). They will be assessed at baseline and 30 days after baseline (study end). The study flowchart is presented in Figure 1 The study started in May 2021.

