**Figure 1 figure1:**
[figure not shown]
Flowchart study design.

The study protocol will be introduced to all participants, the name of the mobile application is not to be communicated in the first step. Previous experience with mobile applications for health will be assessed in all subjects prior to randomization. Randomization is performed by the project leader by using a computer-based randomization algorithm, performing the randomization allocation (ratio 1:1). Each new participant of the study will receive a participant number that corresponds to the following treatment number.

At baseline, participants will complete a series of questionnaires covering sociodemographic and treatment-related information, along with a self-rating (ie, BDI-II) of current symptoms of MDD. An expert will perform a thorough clinical-psychiatric interview and rate participants’ symptoms of depression (ie, HDRS). To assess the current psychophysiological stress response at baseline conditions, a nurse will measure participants’ heart and respiratory rate and blood pressure.

Next, participants will be informed about the study condition assignment. Participants of the control condition will have no additional task to their TAU instruction. Participants of the intervention group will be introduced to the Headspace app and its handling. The necessary timeframe of the baseline assessment will be around 60 minutes.

The intervention group will be required to download the mobile application Headspace and start their daily usage in addition to their TAU (as explained in the “Intervention” section).

Regarding the control group, there will be no intervention planned. The control group will receive the same TAU as the intervention group during inpatient treatment. Participants of both groups will be supported in their outpatient treatment after discharge as usual. Compared to the treatment group, the control group will not be told about the application and its use but will be held on a waitlist. The control participants will be instructed to undergo their TAU (eg, private practice therapist), whereby they will be asked to come to the visit at measurement time T1 after 30 days (see the time points in Table 2).

At T1, both groups will undergo the same procedures as they did at baseline (maximum 60 min). Following the visit, the name of the mobile application will be communicated to the participants of the control group so they can use it after the end of the study as needed.

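### Comparing unadjusted change scores in BDI-II and HDRS leaves unused the precision that adjustment for the already collected baseline score would give

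*Protocol article*

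**What the plan says.** The null hypothesis in the Data Analysis section is worded in changes: "The changes in the BDI-II and HDRS sum scores between baseline and T1 do not differ between the intervention and the control group". The alternative is framed the same way, as T1 against baseline compared between arms. The method sentence then makes change the compared quantity: "When comparing the change scores in the intervention group with those of the control group, typical hypothesis-testing, including mixed linear models, will be used". No baseline covariate and no constraint on the baseline means is named.

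The baseline values will be available. The Study Design section has participants complete baseline questionnaires "along with a self-rating (ie, BDI-II) of current symptoms of MDD", and an expert rates the HDRS at the same visit. There are two assessments only, at baseline and at day 30.

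The sample size is that of a two-sample t test at α=.05 with 80% power: 64 per arm, raised to 140 in total for dropout of up to 10%. On the effect size the article says: "The estimation is based on an expected effect size of Cohen *d*=0.50, which is based on prior published studies of mindfulness-based apps". It gives no SD and no baseline-to-T1 correlation, and it does not say whether d is scaled by the SD of the score or of its change.

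**The concern.** Subtracting baseline fixes its coefficient at 1. ANCOVA estimates that coefficient from the data and so removes more of the outcome variance unless the true slope is 1. The mention of mixed models does not by itself change this. With T0 and T1 as responses and an arm-by-time term, the model returns the difference in mean change on complete data. With the change score as response, each participant has one record per scale and there is nothing to model as random. Only a baseline covariate or a common baseline mean gains the extra precision, and the article names neither.

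At stake is a wider confidence interval on both primary outcomes than the same data could give. Because the scale of d is undefined, it is also unclear how the 80% power relates to the comparison of change that is planned.

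**Working it through.** **Inputs from the article (Data Analysis):** d=0.50, α=.05, power 80%, two-sample t test, 64 per arm, 140 in total, dropout up to 10%. **Assumed, because not given:** rho from 0.3 to 0.8, and equal variance (SD²) at baseline and T1.

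**1. The plan's own figure.** A two-sided two-sample t test (noncentral t) with d=0.50 needs 63.8, so 64 per arm, with power 80.1%. The article does not state sidedness; a one-sided test would need 51, so two-sided is what was used. For dropout, 128/0.9 = 142.2, so 143, close to 140. From 140, losing 10% leaves 126, or 63 per arm, with power 79.5%. That half point comes from rounding and has nothing to do with change scores.

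**2. Variances.**
- Change score: 2(1 − rho)·SD²
- ANCOVA residual: (1 − rho²)·SD²
- Ratio, ANCOVA to change: (1 − rho²)/[2(1 − rho)] = (1 + rho)/2
- Information lost by using change: 1 − (1 + rho)/2 = (1 − rho)/2

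| rho | Change variance (SD²) | ANCOVA variance (SD²) | Ratio | Information lost |
|---|---|---|---|---|
| 0.3 | 1.40 | 0.91 | 0.65 | 35% |
| 0.5 | 1.00 | 0.75 | 0.75 | 25% |
| 0.7 | 0.60 | 0.51 | 0.85 | 15% |
| 0.8 | 0.40 | 0.36 | 0.90 | 10% |

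**3. Power at 64 per arm if d=0.50 is in raw-score SDs.** The standardised effect is 0.50/√[2(1 − rho)] for change and 0.50/√(1 − rho²) for ANCOVA. At rho=0.3 these are 0.50/√1.40 = 0.423 and 0.50/√0.91 = 0.524.

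| rho | Change | ANCOVA |
|---|---|---|
| 0.3 | 66.0% | 83.7% |
| 0.4 | 72.7% | 86.5% |
| 0.5 | 80.1% | 90.0% |
| 0.6 | 88.1% | 93.9% |
| 0.7 | 95.2% | 97.6% |

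The crossing point is rho=0.5, where 2(1 − rho) = 1 and the change score has the same SD as the raw score.

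**4. Power at 64 per arm if d=0.50 is in change-score SDs.** Change scores give 80.1% at every rho. For ANCOVA the standardised effect is 0.50/√[(1 + rho)/2], with power 93.6%, 90.0% and 86.1% at rho=0.3, 0.5 and 0.7. For 80% power ANCOVA would need 42, 49 and 55 per arm.

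The ANCOVA figures use the t test with the residual variance and ignore the one degree of freedom spent on the covariate, which is negligible at this size.

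**The case against.** The strongest reply is that the missing adjustment is partly an inference from silence. The article lists mixed models among its methods and excludes no covariate. A change score regressed on arm and baseline gives the same arm estimate and standard error as the T1 score regressed on arm and baseline, so the word change does not rule ANCOVA out. The article condenses a fuller protocol, and a covariate list can be left to an analysis plan that is not shown. What stands of this: an adjusted analysis remains compatible with the text. But both hypotheses, the method sentence and the two-sample t test used for sizing all describe the unadjusted comparison, and that stated choice can be improved.

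Stronger readings are tempting, and the article does not support them:

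- *A reader might infer that the trial is underpowered.* That needs d in raw-score SDs and rho below 0.5. Neither is stated. Reading d on the variable being compared is at least as natural, and power is then as claimed.
- *A reader might take a loss of 15–35% as fact.* It is (1 − rho)/2 for an assumed rho of 0.7 down to 0.3; a higher rho gives a smaller loss.
- *A reader might see bias through regression to the mean.* Allocation is randomised, so the change contrast is unbiased over randomisations and type I error is unaffected. Chance baseline imbalance bears on precision and on the estimate in the realised sample.
- *A reader might argue that mixing discharged patients and outpatients lowers rho.* Differing severity widens the spread between participants and may equally raise it.

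**Conclusion.** The point holds as a free gain in precision. The article compares changes in BDI-II and HDRS and names no use of the baseline score beyond subtraction. With equal variances, ANCOVA is more precise at any rho below 1. The size depends on a correlation that the article does not give: at the assumed values in the table, 10% to 35% of the information is lost.

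The point does not establish a bias, and it does not establish an error in the 80% power. The sample size reproduces. Whether it delivers 80% for change scores turns on the undefined SD behind d=0.50: yes at 64 per arm if it is the change-score SD, and only for rho of about 0.5 or more if it is the raw-score SD (about 66% at rho=0.3). The case for ANCOVA does not depend on which reading is right.

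**What to change.** State the primary analysis for each scale as the T1 score regressed on arm and the baseline score of the same scale, and report the adjusted mean difference with its 95% CI. A longitudinal model with T0 and T1 as responses and a common baseline mean would serve equally. Its further advantage of keeping participants who have only a baseline record is limited here, because the Participants and Recruitment section has the data of withdrawn participants destroyed. Use the same form for heart rate, blood pressure and respiratory rate, and keep raw change scores as description.

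In the sample-size paragraph, say whether d=0.50 is in SDs of the score or of its change.

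The cost is wording only: no new data, no extra visits and no change to the sample size. The article reports 30 participants enrolled as of December 2021 out of a planned 140, so at that stage the wording could be settled before any comparison of outcomes.

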### Participants and Recruitment

In total, 140 patients should be recruited (70 for the intervention and control group each).

Inclusion criteria: inpatients or partial inpatients (day clinic, at least 18 years old, before discharge to ambulatory care as well as outpatients, all diagnosed with MDD according to the International Classification of Diseases. All participants must have a smartphone and be generally willing to download and use a mindfulness-based app for at least 30 days.

Exclusion criteria: Acute suicidality, dementia, acute substance dependency, psychotic, schizophrenic, or schizoaffective disorders, serious health conditions like unstable cardiovascular, heart, lung, endocrine or neurological disorders, and momentary use of Headspace.

The study will be brought to the attention of potentially eligible patients of the UPK through their health care providers at UPK and through the study flyer. If they show interest in participating, the patients will receive a document with all the required information regarding the study in order to give their informed consent. After the patients sign the form of consent, it will take between 1 to 7 days until they will get scheduled for their first appointment. This will give them an adequate amount of time to consider their participation carefully. Participants will be informed about the scope and procedure of the study. Their written informed consent will be obtained.

The participants can be withdrawn from the project for any of the following reasons:

At their own request (withdrawal of consent)In case of nonadherence to the study protocol (if participants use the app on less than 25 days or if they use other courses beyond the basic course)If one or more exclusion criteria appear within the time of observation

If a participant wants to discontinue participation, this will be accepted without the need for reasons. However, the participant will be asked for potential reasons for discontinuation to document it for further analysis. The date and, if available, the reason for the withdrawal will be documented, and the participant‘s data will be destroyed.

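### Minor arithmetic slip: 140 randomised with the full 10% dropout leaves 63 per arm (79.5% power), one short of the 64 per arm the plan requires

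*Protocol article*

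**What the plan says.** All the planning inputs stand in the protocol article.

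- **Effect size** (Data Analysis): "The estimation is based on an expected effect size of Cohen *d*=0.50".
- **Error rates** (Data Analysis): α = .05 and β = .2, that is 80% power. Sidedness is not stated.
- **Required size** (Data Analysis): "the required sample size for a two-sample *t* test is 64 for each group".
- **Dropout and total** (Data Analysis): "The dropout rate is expected not to exceed 10%, resulting in 140 patients overall". No inflation formula is given.
- **Per-arm target** (Participants and Recruitment): "In total, 140 patients should be recruited (70 for the intervention and control group each". Study Design gives the allocation ratio as 1:1.

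Participants and Recruitment also lists nonadherence among the reasons for which a participant can be withdrawn. It defines this as using the app on fewer than 25 days or using courses beyond the basic one. Data Analysis does not define dropout or mention these withdrawals.

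**The concern.** The total is presented as the result of allowing for dropout of up to 10%. A reader will therefore take it that 140 still yields the required 64 per group when 10% are lost. It does not. The 64 is the smallest per-arm number that reaches 80% power by the named test, so there is no slack to absorb a shortfall.

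Little is at stake in power. What matters is that a stated derivation should follow from its own inputs, and the last step of this one does not.

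The withdrawal rule raises a related but separate question. Its criteria concern app use, so in practice they can remove participants only from the intervention arm. If those removals come on top of the 10%, the evaluable number falls further and unequally between arms. The article does not say whether they do.

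**Working it through.** **1. Reproduce the plan's 64.** Inputs from Data Analysis: d = 0.50, α = .05, power 80%, two-sample t test. I take α as two-sided, because that reproduces 64; one-sided would need 51.

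Power comes from the noncentral t distribution with 2n − 2 degrees of freedom and noncentrality d × √(n/2). Solving for 80% gives n = 63.77, rounded up to **64 per group**, or 128 in total. This matches the plan.

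**2. Apply the stated dropout to the stated total.**

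- 140 × (1 − 0.10) = 126
- 126 / 2 = **63 per arm**, one below 64

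**3. Power at the relevant sizes** (t test, d = 0.50, two-sided .05).

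| Per arm | Power |
|---|---|
| 63 (10% lost from 70) | 79.5% |
| 64 (plan's requirement) | 80.1% |
| 70 (no dropout) | 83.6% |

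The shortfall at 63 is 80 − 79.5 = 0.5 percentage point against the 80% target.

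**4. Dropout that 140 can absorb.** 1 − 128/140 = **8.6%**. The requirement fails only for dropout between 8.6% and 10%.

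**5. What full inflation would give.**

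- On the total: 128 / 0.9 = 142.2, so 143
- Per arm: 64 / 0.9 = 71.1, so 72 per arm, or 144

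The plan is therefore 3 to 4 participants short of a total that covers 10%. One possible origin is multiplying instead of dividing: 128 × 1.1 = 140.8, rounded down to 140. Because the article gives no formula, this is an inference.

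**6. Illustration for the withdrawal rule, kept apart from the above.** The article gives no nonadherence rate, so the rates below are assumptions. Start from 63 per arm, hold the control arm at 63, and remove a further share of the intervention arm.

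| Assumed further loss, intervention arm | Evaluable, intervention vs control | Power |
|---|---|---|
| 20% | 63 × 0.8 = 50.4, so 50 vs 63 | 74% |
| 30% | 63 × 0.7 = 44.1, so 44 vs 63 | 71% |
| 50% | 63 × 0.5 = 31.5, so 32 vs 63 | 63% |

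These figures show sensitivity only. They do not predict what will happen in this trial.

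**The case against.** The strongest reply is that the slip is immaterial. Power of 79.5% rounds to the stated 80%, and 140 is within 3% of 143 and 144. Ten per cent is a ceiling rather than an expected value, and at 8.6% or less the requirement is met. All of this stands, and it is why the point is minor.

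A second reply is that the normal approximation needs only 63 per group, gives 80.1% power there, and inflates to exactly 63 / 0.9 = 70 per arm. That is true arithmetically, but it is not the plan's derivation: the article names the t test and states 64.

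A reader might go further and infer that the trial is underpowered. The documents do not support that. The 80% is attached to 64 per group, and 140 misses this by one participant per arm, only near the dropout ceiling and with losses split equally between arms.

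A reader might also infer that the withdrawal rule will cut power to 74% or lower. That does not follow either. The article says participants can be withdrawn, which is permissive. The Intervention section provides weekly contact and reminders to support daily use. Since dropout is undefined, the 10% may already include such withdrawals. What remains is that the article does not say.

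**Conclusion.** Wrong as written, and minor. At the plan's own dropout ceiling, 140 randomised gives 63 evaluable per arm where the plan requires 64, and power is 79.5% instead of at least 80%. This rests on two-sided α, d = 0.50 and equal dropout in the two arms. No change to the design follows from it.

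The coverage of the 10% is a matter of unclear definition. Whether nonadherence withdrawals fall inside or outside it cannot be determined from the article, and any power loss from them depends on rates the article does not give.

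**What to change.** Keep 140 and replace the dropout sentence with, for example:

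> With 140 randomised and 10% dropout, 63 per arm are evaluable, giving 79.5% power for d = 0.50 (80% if dropout is at most 8.6%).

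This costs one sentence and a slightly less favourable stated power. No extra enrolment is needed. If the sponsor prefers the total to cover the full 10% strictly, it becomes 143, or 144 with equal arms.

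Separately, state what the 10% covers and reconcile it with the withdrawal reasons in Participants and Recruitment. The clean solution is to keep participants who do not adhere in follow-up and in the analysis, so that the 10% means a missing T1 assessment only. This is a larger step than the sentence above, because it changes the withdrawal criteria of an approved trial that is already enrolling (30 participants as of December 2021). The arithmetic correction does not depend on it. If power under nonadherence losses is reported, label the assumed rates as assumptions.

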### Ethics Considerations and Approval

This study will be conducted according to the international standards of the Declaration of Helsinki and subsequent amendments. This trial will be performed in compliance with the study protocol and with good clinical practice guidelines.

The study protocol has been approved by the Swiss Ethics Committee (North/Central Switzerland-EKZN; 2021-00452) and follows the guidelines of the Declaration of Helsinki and current Swiss legislation on privacy and data protection. The study participants will sign the written informed consent form before randomization. Participants will be provided with detailed information about the study and will be informed that they may leave the study at any time.

## Results

This study was funded in February 2021 and approved by the institutional review board on April 15, 2021, and it started in May 2021. As of December 2021, we have enrolled 30 participants. The findings are expected to be published in spring 2023.

The potential immediate benefit for the participants consists of a decrease in symptom severity and prevention of depressive relapse without side effects. The long-term benefits are that patient care, especially in the outpatient setting or after discharge from inpatient treatment, will be easily augmented and improved. Moreover, the patients will be supported by an easily accessible mindfulness-based intervention. Such benefits may accommodate the issue of limited capacities in ambulatory care. With the prevention of depressive relapse, people with MDD get the chance to not only improve in symptom severity but also to live in their homes, with their families, go to school, or to work, accompanied by a tool for stress reduction.

## Abbreviations

BDI-II: Beck depression inventory II
HDRS: Hamilton Depression Rating Scale
MBI: mindfulness-based intervention
MDD: major depression disorder
TAU: treatment as usual
UPK: University Psychiatric Clinics
